### Sample size

A sample size calculation for comparing two means with unpaired t-tests based on the reductions in the prevalence of chemotherapy-induced nausea reported by Panahi et al. [49], estimates that 73 participants would be required in the intervention and control groups (i.e. total of N = 146) to detect this difference with 80 per cent power at the 95 per cent significance level (two tailed).

Approximately 250 patients receive moderately emetogenic chemotherapy and 240 patients receive highly emetogenic chemotherapy at Princess Alexandra Hospital each six months (1/3-1/9/2012) which indicates that the required sample size is obtainable in this study.

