### Withdrawal criteria

Any participant who has been randomised and then withdraws will be included in the study on an intention to treat basis with patient consent. If a participant withdraws consent, data will be collected up until their time of withdrawal. Primary outcome data will be collected in these participants where possible.

Any participant who withdraws before being randomised (i.e. allocated to a particular study treatment) will be replaced, so that the next consenting participant receives the randomisation sequence and that participant’s allocated study treatment.

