### Statistical analysis

Analyses will be conducted according to intention-to-treat principles i.e. the consent process will maximise outcome data collection and attempt to assess nausea symptoms for everyone, and will retain original group allocation despite actual compliance levels.

Participants will be block stratified by chemotherapy category (i.e. minimal, low, moderate and high emetogenicity) then randomised within strata into intervention and control groups (Figure 1) [48].

Descriptive statistics will be presented as mean ± standard deviation, or median with range, as appropriate. Parametric analyses will be used for all continuous variables. Chi-square analyses will determine associations between categorical variables. For example, the incidence, severity and type of nausea and vomiting between the two groups. Pearson correlation analysis of continuous variables will be performed. Repeated measures analyses will be conducted to detect between group differences over time as per our statistician recommendations. Statistical significance will be set at p < 0.05 level (two-tailed). Data will be analysed using SPSS for Windows version 22 (Statistical Package for Social Sciences, IL, USA).

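### The sample size sets a two-means t-test on a reduction in prevalence and has no margin for loss, so its 80% power is not shown to apply to the primary nausea outcome

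*Protocol article*

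**What the plan says.** The Sample size section describes the calculation as "comparing two means with unpaired t-tests based on the reductions in the prevalence of chemotherapy-induced nausea", the reductions being those reported in a cited previous trial. It "estimates that 73 participants would be required in the intervention and control groups (i.e. total of N = 146"), and the claim is that this number suffices "to detect this difference with 80 per cent power at the 95 per cent significance level (two tailed").

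Elsewhere in the protocol article:

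- Primary outcomes lists the frequency, severity and duration of acute and delayed nausea. Prevalence is not listed. The questionnaire section says that nausea is recorded on the five-point items of the INVR.
- Statistical analysis states: "Repeated measures analyses will be conducted to detect between group differences over time". It also plans parametric analyses for continuous variables and chi-square analyses for categorical ones, with incidence of nausea among the examples. It sets significance at p < 0.05, two-tailed.
- Withdrawal criteria states: "Any participant who has been randomised and then withdraws will be included in the study on an intention to treat basis". Only people who withdraw before randomisation are replaced. Primary outcome data from later withdrawals are collected where possible.
- Study duration takes each participant to four days after the third chemotherapy session.

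**The concern.** A t-test on two means is sized from a mean difference and a standard deviation. A reduction in prevalence is a difference between two proportions. The sentence names one and takes its effect from the other, so a reader cannot tell which calculation gave 73.

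The power is also attached to a quantity that is not the declared primary outcome, and to a single unpaired comparison, although group differences over time are to be tested by repeated measures across three cycles.

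Separately, the number required and the stated total coincide, while the protocol itself foresees withdrawal after randomisation.

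What is at stake is how the result is read. If the trial finds no difference in nausea scores, readers will take it as a result with 80% power on the primary outcome, and nothing in the document supports that figure for that outcome.

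**Working it through.** **Inputs from the protocol article.** 73 per arm, 146 in total, 80% power (Sample size); two-sided α of 0.05 (Statistical analysis). The article gives no mean difference, SD, pair of rates or loss rate, so 73 cannot be reproduced forwards. It can only be back-solved.

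**1. What 73 per arm detects as a comparison of means.** With n = 2(z₀.₉₇₅ + z₀.₈₀)²/d²:

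d = (1.960 + 0.842) × √(2/73) = 0.464.

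The noncentral t calculation gives d = 0.467. So 73 is a possible answer to a two-means calculation, for a standardised difference of about 0.47.

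**2. What 73 per arm detects as a comparison of proportions.** Take 60% as an illustrative control rate; the Background puts CINV at upwards of 60% of patients. For 60% against 37%, the mean rate is 0.485 and the pooled two-proportion formula without continuity correction gives:

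n = [1.960√(2 × 0.485 × 0.515) + 0.842√(0.60 × 0.40 + 0.37 × 0.63)]² / 0.23² ≈ 3.86/0.0529 ≈ 73.

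Other illustrative pairs that give about 73 are 80% against 58.8% and 40% against 19.0%. With continuity correction these pairs need 82 to 83 per arm.

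**3. Does the choice of test move the number?** For 60% against 37%, the two-means formula with the binomial variance (0.24 + 0.2331)/2 = 0.2366 gives n = 2 × 7.849 × 0.2366/0.0529 ≈ 70.2, that is 71 per arm. Against 73, the mix of scales barely changes N if the input really was a difference in prevalence. The main defect is therefore the link to the endpoint, not the arithmetic.

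**4. Link to the repeated measures analysis.** As an illustration, suppose the same d = 0.464 in each cycle, an average over three cycles, and compound symmetry with correlation ρ. The variance factor is (1 + 2ρ)/3:

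- ρ = 0.3: factor 0.533, power about 97%
- ρ = 0.5: factor 0.667, power about 93%
- ρ = 0.7: factor 0.800, power about 88%

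The figure of 80% describes none of these. The real value depends on the INVR difference, its SD and the correlation, and the article gives none of them.

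**5. Margin for loss.** 2 × 73 = 146, so the margin is zero. For the single two-group comparison at d = 0.467, with 73 randomised per arm and assumed loss rates (noncentral t):

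- 10% loss: 66 per arm analysed, power 76%
- 20% loss: 58 per arm analysed, power 70%
- 30% loss: 51 per arm analysed, power 65%

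For scale only, holding 80% for that comparison would take 73/0.9 → 82 per arm (164 in total), 73/0.8 → 92 (184) or 73/0.7 → 105 (210).

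**The case against.** The strongest reply has four parts.

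**The power does fit an analysis in the plan.** A reader might infer that the 80% belongs to no planned analysis. The document does not support that. A prevalence-based 73 would suit the planned chi-square comparison of incidence, without continuity correction, and an unpaired t-test falls under the parametric analyses. This stands. It does not rescue the claim for the primary outcome, because incidence is not listed there.

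**No wrong number has been shown.** This also stands. The sum is correct, 73 is attainable on either scale, and the choice of test moves it by about two per arm. A condensed article may leave rates, SD and expected loss to the full protocol, so their absence alone is no finding. The finding is that the sentence, as printed, joins a test to an effect of another kind and ties the power to that effect.

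**The trial may not be underpowered.** A reader might infer a shortfall on the nausea scores. The document does not support that either: under the assumptions in step 4, repeated measures would give more than 80%. The losses in step 5 apply only to the single comparison.

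**Withdrawal is not the same as missing data, and 146 may be the number analysed.** Withdrawals stay in the intention-to-treat analysis and the team intends to maximise data collection. No sentence says that recruitment stops at 146. This softens the point without removing it: data after withdrawal are collected only where possible, and the natural reading of the text is a total of 146 with no margin.

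**Conclusion.** The concern holds in this form. The Sample size section sets a two-means t-test on a reduction in a proportion, and neither the test nor the effect corresponds to the primary nausea outcome or to the repeated measures analysis. The stated 80% power is therefore not shown to apply to the primary analysis; its true value there is unknown and could lie on either side of 80%.

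The absence of a margin is a separate defect, not the cause of the mismatch. For the comparison on which the trial was sized, 80% requires complete data; power is about 76% at 10% loss and 70% at 20%. These figures rest on assumed loss rates, on d = 0.467 back-solved from 73 per arm, and on reading 146 as the number randomised.

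The phrase "80 per cent power at the 95 per cent significance level (two tailed") is a clerical slip, since Statistical analysis sets p < 0.05.

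**What to change.** Rewrite the Sample size section so that it:

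- names one primary nausea endpoint, its time point and the planned analysis that tests it;
- puts effect and test on the same scale, with an assumed difference and SD if a nausea score is meant, or the two rates and a two-proportion test if incidence is meant;
- gives the correlation assumed between cycles, if the repeated measures analysis is the one being powered;
- says whether 146 is the number randomised or analysed, and restates the power that 146 randomised delivers at the team's own expected loss;
- replaces 95 per cent with 5 per cent for the significance level.

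If a standardised difference of 0.47 is quoted, describe it only as what 73 analysed per arm can detect in a single two-group comparison. It is not an expected effect on the INVR, and the loss rates used above should not be copied into the protocol as if they were estimates.

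The cost is protocol wording and a short recalculation. No extra patients are required. The stated power may become less favourable, or more so, depending on the inputs.

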### Ethical considerations

The study protocol has been approved by the Metro South Human Research Ethics Committee on the 4th of July, 2013. The trial has also been registered with the Australian New Zealand Clinical Trials Registry and has been assigned the identifier, ACTRN12613000120774. The study complies with the Declaration of Helsinki rules and the principles of Good Clinical Practice guidelines. Informed consent will be gained from all participants before commencing the trial and patient data will be stored securely. Participants will also be monitored for adverse effects and will be discontinued immediately if the study protocol is determined to be causing harm or if the participant chooses to withdraw. This study received grant funding from the Queensland Health – Health Practitioner Scheme.

## Discussion

This study protocol expands on the current literature regarding the efficacy of ginger as an adjuvant therapy for CINV. Recommendations for the use of ginger in the oncology setting are premature, as previous reviews have shown inconsistent results and have possessed several limitations. Primary concerns identified in the literature include the lack of control of anticipatory nausea, the inconsistent use of standardised ginger extracts and validated assessments tools, and a lack of assessment for prognostic factors that may influence individual CINV response [21]. Additionally, recent pharmacokinetic studies demonstrate that the half-life of the active compounds within ginger are relatively short-lived, which suggests that the dosing regimens employed by previous studies may be suboptimal. Furthermore, multiple studies included in these reviews have used anti-emetic therapies that are not congruent with current best practice and anti-emetic guidelines and therefore, the application of these previous findings to current practise are further diminished [21,48].

In designing our trial, we aimed to address these limitations while incorporating elements of rigorous study methodology that have been incorporated in previous trials in this area. For example, our trial will be using multiple, validated assessment tools along with a standardised ginger extract, both of which have been utilised in at least two previous trials [50,51]. We will, however, expand on this by independently analysing our extracts at both the beginning and end of our recruitment phase to ensure consistent potency.

It should also be noted that one study by Ryan et al. [51] found ginger to reduce CINV when ginger supplementation was commenced three days before chemotherapy. We, however, decided against using this methodology and opted for ginger supplementation commencing on the day of chemotherapy due to the following reasons. Firstly, there have been multiple previous trials using ginger for CINV as well as other forms of nausea that did not use the regimen used by Ryan et al. [51] but rather a timeframe and dosage more closely resembling the regimen in our protocol that yielded beneficial results [49,52-54]. In addition to this, to date, there has been no research that has investigated the regimen used in the Ryan et al. [51] study compared to the more typical dosing regimen that has been employed in our study, which restricts one from determining the superiority of said regimen. Lastly, the basis for said regimen, from our research and from the discussion in the Ryan et al. [51] paper, seems to have been implemented largely on a theoretical basis and therefore, until more evidence arises, we have decided to instead opt for the more patient-convenient regimen described in this manuscript.

Our trial will also be the first to introduce multiple novel study design elements. Primarily, our study will be the first to recruit only chemotherapy-naive patients. This strategy should mitigate the significant limitation of anticipatory nausea. It is a response to previous research reporting that CINV control progressively deteriorates with each subsequent chemotherapy cycle, if not adequately controlled during the initial cycle [35]. Due to the association between fatigue and nausea in this setting, we will also investigate the effect that ginger has on this association in order to determine if ginger may be of benefit to patients also experiencing cancer-related fatigue. Finally, our study will also implement a dosing regimen that is consistent with the findings of the previously mentioned pharmacokinetic studies that will likely improve the CINV protection of this therapy. If successful, this trial will provide support for the efficacy of ginger as a viable adjuvant anti-emetic therapy and in doing so, help manage chemotherapy symptoms and assist in improving patient QoL.

## Abbreviations

CINV: Chemotherapy-induced Nausea and vomiting; QoL: Quality of life; PG-SGA: Patient generated - subjective global assessment; FACT-G: Functional assessment of cancer therapy- general; FACIT-F: Functional assessment of chronic illness therapy-fatigue; INVR: Rhodes inventory of Nausea vomiting and retching; ESAS: Edmonton Symptom Assessment System; FLIE-5DR: The functional living Index – Emesis – 5 day recall.
